**Design:**

This multi‐center, assessor‐blinded clinical trial will examine QEEG biomarkers as predictors of rTMS treatment responsiveness in 25 patients with mild cognitive impairment (MCI). Adults aged 60 years or older will undergo cognitive assessments using the Montreal Cognitive Assessment (MoCA) or mini‐mental state examination (MMSE) and have an electroencephalography (EEG) recording. Participants will complete 10 rTMS sessions targeting the left DLPFC over 2 weeks, with 2000 pulses per session at 20 Hz. Cognitive tests will be repeated post‐treatment, and participants will be classified as responders or non‐responders based on cognitive changes, then baseline QEEG parameters will be compared between the two groups. The primary endpoint is the proportion of responders at ten sessions after rTMS (score post‐intervention > score pre‐intervention = responder, according to the minimal clinically important difference (MCID) threshold (i.e., an increase of at least 3 points or 10% on the MMSE, or an increase of at least 1 point on the MoCA); score post‐intervention ≤ score pre‐intervention = non‐responder). The secondary endpoints are the differences in baseline QEEG features between responders and non‐responders.

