## Study Design

1

This pilot, multicenter, assessor‐blinded study recruited adults aged ≥60 years from the Tabari cohort registry. After cognitive screening at Imam Hospital, eligible participants underwent baseline EEG recording. Two weeks later, they received 10 sessions of high‐frequency rTMS (20 Hz) over the left DLPFC at the psychiatrist's clinic. Post‐intervention cognitive testing was performed to classify responders and non‐responders (Fig. 1). The full procedural sequence of the study procedure is described in detail below.

This study design as shown in (Figure 1).

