#### Questionnaires

1.4.1

After 10 rTMS sessions, we will perform the cognitive tests again under the same conditions. For educated individuals, we will use MoCA exams, and for uneducated subjects (0 years of schooling), we will only use the MMSE test again. If a participant's MMSE or MoCA score increases after the TMS, they will be considered a responder. Conversely, if their score decreases or there are no changes, they will be classified as a non‐responder (Kayasandik et al. 2022).

We will utilize the minimal clinically important difference (MCID) to evaluate significant changes in test scores. According to the MCID, an increase of 3 points or 10% (Borland et al. 2022; Watt et al. 2021) in the MMSE indicates cognitive improvement (Borland et al. 2022; Watt et al. 2021). The MCID for the MoCA may vary, but we will consider a 1‐point increase as a sign of cognitive improvement (Lindvall et al. 2024). After completing the work, patients will receive free visits from the psychosomatic fellowship to continue their treatment in accordance with ethical principles.

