### Group Classification

1.5

MCI with 22 < MoCA < 26 or 20 < MMSE < 24 after 2 weeks of intervention and post‐assessments will be divided into two groups (score post‐intervention > score pre intervention = responder, according to MCID threshold (i.e., an increase of at least 3 points or 10% on the MMSE, or an increase of at least 1 point on the MoCA); score post‐intervention ≤ score pre‐intervention = non‐responder).

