#### Primary Endpoint

1.7.1

All assessors will be blinded to group allocation and receive data labeled as “group A” and “group B.” Statistical analyses will be conducted using StataNow18.5 (Stata Corp, College Station, TX, USA), adhering to CONSORT guidelines. Normality of continuous variables will be checked using skewness and kurtosis, with variables considered non‐normal if absolute skewness > 2 or kurtosis > 3. Baseline characteristics, including (sex, hyper‐lipidemia, hypothyroid, hyper‐tension, diabetes, smoking, ischemic heart disease, education, and age) will be compared between groups using Fisher's exact test for categorical variables and the Mann–Whitney *U* test for non‐normal continuous variables. For normally distributed continuous variables, between‐group comparisons will be performed using the independent samples t‐test.

Initially, paired *t*‐tests (a suitable transformation or non‐parametric test) or equivalents for non‐normal data will be used to evaluate overall pre‐ to post‐rTMS changes within all 25 participants, assessing global treatment efficacy and identifying cognitive subdomains demonstrating the greatest response. Subsequently, participants will be categorized into responders and non‐responders based on MCID criteria. Between‐group comparisons of cognitive scores and subdomains will then be performed using ANOVA for baseline and ANCOVA for post‐intervention outcomes, adjusting for baseline scores and potential confounders. Pre‐intervention values refer specifically to baseline cognitive test scores, totally and in each cognitive sub‐domain, and related continuous variables measured before rTMS, which serve as covariates in the analyses. The QEEG features are analyzed separately as part of the secondary endpoint assessment. For non‐normal variables, suitable transformation will be applied, and median differences with percentage changes reported. Marginal plots from ANCOVA will visualize adjusted group differences post‐intervention. This two‐stage analytical approach allows comprehensive evaluation of rTMS effects both globally and within clinically meaningful responder groups across cognitive domains.

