Besides, there are some limitations to this protocol study. As an open‐label trial, it is subject to significant confounds, including treatment expectations on the part of participants, but this is a methodological limitation intrinsic to an open‐label trial (Thase 2001). For the future direction, more analysis with a larger dataset will be recommended, and randomized, sham‐controlled study can affect the generalizability and reliability of the outcomes. Additional predictive biomarkers such as genetic factors, neuroimaging, or biochemical biomarkers can be noticed in future study.

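### The only assessor blinding described is to a group allocation that this single-arm trial does not have, so it cannot protect the cognitive rating behind the primary endpoint

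*Protocol article*

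**What the plan says.** The title carries both labels, assessor-blinded and open-label. The abstract (Design) repeats the first: "assessor‐blinded clinical trial will examine QEEG biomarkers as predictors of rTMS treatment responsiveness in 25 patients". Section 1 uses it again.

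Section 1.7.1 is the only place that says what the blinding consists of: "All assessors will be blinded to group allocation and receive data labeled as" group A and group B.

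On treatment, the abstract says "Participants will complete 10 rTMS sessions targeting the left DLPFC over 2 weeks". Section 1.3.1 gives one stimulation protocol for everyone, and no sham or control arm is described.

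On assessment, Section 1.4.1 says that after the tenth session "we will perform the cognitive tests again under the same conditions". Section 1.5 then forms the groups by comparing post with pre scores: "score pre intervention = responder, according to MCID threshold". The threshold is at least 1 point on the MoCA, or at least 3 points or 10% on the MMSE. Section 1.6.1 makes the proportion of responders the primary endpoint.

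Among the confounds of an open-label trial, the Discussion (Section 2) names expectation: "including treatment expectations on the part of participants".

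**The concern.** Assessor blinding is useful when the person who scores the outcome could otherwise be swayed by knowing the treatment or expecting a result. In this design that person is the MoCA or MMSE rater at the post-treatment visit. The blinding in Section 1.7.1 is aimed at group membership, which does not exist until that rater has scored the test.

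The stakes are the primary endpoint and how it is read. For participants tested with the MoCA, one point separates a responder from a non-responder, so a small systematic shift in scoring changes the proportion. The same labels define the two groups whose baseline QEEG is compared in Section 1.7.2. A reader who sees the label in the title may give the responder proportion a protection that the described procedure cannot supply.

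**Working it through.** The plan gives no figure to reproduce on this point. The check is first one of logic and then an illustration of sensitivity.

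**Step 1: is there an allocation to be blind to?** All participants receive the same 10 active sessions (abstract; Section 1.3.1). Section 1.7.1 first analyses "rTMS changes within all 25 participants" as one group and only afterwards splits them into responders and non-responders. There is one arm and no allocation.

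**Step 2: when do the groups arise?** The order in Sections 1.4.1, 1.5 and 1.7.1 is: treatment, post-treatment test, comparison with baseline, group label. The rater's score is an input to the label, so a label applied later cannot have masked the rater.

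**Step 3: whom can the A/B labels mask?** Section 1.7.1 compares post-treatment scores between the groups by ANCOVA with the baseline score as covariate. Whoever runs that analysis holds both scores and can see which letter means responder. Someone who compares QEEG features without the cognitive scores (Section 1.7.2) could be masked by the labels.

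**Step 4: what masking would bear on the rater?** In a single-arm pre/post design it would be masking to visit or to the baseline score. The article describes neither.

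**Step 5: how sensitive is the endpoint?**

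Inputs from the article: MoCA threshold 1 point; MMSE threshold taken as 3 points; 25 participants. The 10% alternative gives the same MMSE threshold within the eligible scores of 21 to 23: 10% is 2.1 to 2.3 points, hence 3 on a whole-point scale.

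Inputs assumed, not in the article: SD of the pre-post change 1.5 to 2.5 points; no true mean change; average upward rater drift of 0, 0.5 or 1 point.

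For a whole-point change score approximated by a rounded normal,

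P(responder) = 1 − Φ((threshold − 0.5 − drift) / SD).

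Example: MoCA, SD 1.5, no drift: 1 − Φ(0.5/1.5) = 0.369. With 1 point of drift: 1 − Φ(−0.5/1.5) = 0.631.

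| Rule | SD | Drift 0 | Drift 0.5 | Drift 1 |
|---|---|---|---|---|
| MoCA ≥ 1 | 1.5 | 0.369 | 0.500 | 0.631 |
| MoCA ≥ 1 | 2.0 | 0.401 | 0.500 | 0.599 |
| MoCA ≥ 1 | 2.5 | 0.421 | 0.500 | 0.579 |
| MMSE ≥ 3 | 1.5 | 0.048 | 0.091 | 0.159 |
| MMSE ≥ 3 | 2.0 | 0.106 | 0.159 | 0.227 |
| MMSE ≥ 3 | 2.5 | 0.159 | 0.212 | 0.274 |

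If all 25 took the MoCA, a drift of 0.5 point adds 0.079 to 0.131, or 2.0 to 3.3 patients. A drift of 1 point adds 0.158 to 0.262, or about 4 to 7 patients. On the MMSE a drift of 1 point adds 0.111 to 0.121, about 3 of 25. Widening the SD to 3.0 gives 0.434, 0.500 and 0.566 for the MoCA, the same pattern.

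**The case against.** The strongest reply is that the article is silent on who rates and how, and silence in a condensed article is no evidence of an unmasked rater. This stands. No passage says that the rater sees the baseline sheet, knows the visit or delivers treatment. Section 1 places cognitive screening at a hospital and rTMS at a separate clinic, and Section 1.3.1 has PhD students monitor the sessions, which is compatible with a separate rater. A reader might infer that the rater is blind to nothing and the endpoint has no protection at all; the text does not support going that far. It does not rescue Section 1.7.1, however. That section states a target for the blinding, and no fuller document can make the target exist in this design.

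A second reply is that the sentence in Section 1.7.1 really describes people who receive coded data after classification. That is a sensible reading, and it gives the labels some value for the QEEG comparison. But then the sentence concerns analysts, and nothing is left to support the label in the title.

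Third, a reader might infer that the authors claim to have removed rater bias. They do not say so. The title also says open-label, and the Discussion introduces participant expectation with a word that leaves the list open. The fair statement is that rater expectation goes unnamed beside a label that suggests it was dealt with.

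Fourth, it is tempting to say that rater drift would create a false QEEG finding. The article does not support this. No passage says that raters know the QEEG, and leniency unrelated to it would misclassify patients and tend to blur a difference.

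Finally, this is a pilot, and Section 4 asks for cautious reading. But the article also wants effect-size estimates to plan later trials, and drift in the responder proportion would carry into them.

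**Conclusion.** The point holds in this form: the blinding that the article describes is to an allocation that does not exist. It therefore cannot protect the cognitive rating that produces the primary endpoint, and no masking of the rater to visit or baseline score is described. This rests on the article's own text and on no assumption.

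The size is illustrative. With an assumed change SD of 1.5 to 2.5 points and no true change, the MoCA responder proportion is 37-42% without drift, 50% with 0.5 point and 58-63% with 1 point. The MMSE rule moves less, from 5-16% to 16-27% with 1 point. These figures need an average shift across patients, not one lenient call, and the article gives no evidence that any drift occurs. The starting 37-42% reflects retest noise against a 1-point threshold, which is a separate matter.

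**What to change.** 1. Remove the assessor-blinded label, or redefine it to the masking actually in place, in the title, the abstract, Section 1 and Section 1.7.1.
2. In Section 1.7.1, limit the group A/B statement to those who analyse the QEEG comparison without holding the cognitive scores, and drop the reference to allocation.
3. In the Discussion, name rater expectation beside participant expectation.
4. Where post-treatment testing is still to come, withhold the baseline score and sheet from the post-treatment rater.
5. Where written sheets were kept, rescore them in shuffled order with visit and date removed, as a sensitivity check on the responder classification.

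Items 1 to 3 are changes of wording and can be made even if testing is over, which the past tense in Section 1 ("blinded study recruited adults aged") leaves possible. Their cost is the loss or narrowing of a favourable label. Item 4 needs only a handling rule for the sheets. Item 5 costs staff time and depends on sheets that the article does not say were retained. Items scored live can be masked only in part, so it is a supplement and not a replacement for correcting the label.

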#### Secondary Endpoint

1.7.2

Topographic maps will be generated for each QEEG feature (e.g., absolute power, relative power, power ratio, peak frequency, amplitude asymmetry, coherence, and phase lag) for both responder and non‐responder groups using Neuro Guide software, then calculate the average QEEG features for each group using Neuro Guide. Subsequently, the statistical significance of the dissimilarity between the two groups' EEG topographic maps will be determined using independent *t*‐tests or the Mann–Whitney *U* test, depending on the normality of the variables. ROC analysis estimating Area Under the Curve (AUC), sensitivity (SN), specificity (SP), positive predictive value (PPV), negative predictive value (NPV), A positive likelihood ratio (LR+), and the negative likelihood ratio (LR‐) for optimal cut‐points, as well as comparing AUC across biomarkers, will be performed using Stata 18 software. These diagnostic accuracy measures specifically assess the predictive ability of QEEG biomarkers in distinguishing responder from non‐responder status.

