## Limitations

4

One key limitation of this study is the relatively small sample size, particularly in the context of post hoc stratification into responders and non‐responders. Given the exploratory nature of the study and the anticipated imbalance in group sizes, the statistical power to detect large between‐group differences is limited. As such, the findings should be interpreted with caution and viewed primarily as preliminary indications of potential QEEG biomarkers associated with treatment response. This limitation constrains the generalizability of the results and precludes definitive hypothesis testing. However, this study serves as a pilot investigation intended to generate effect size estimates and feasibility data that will inform the design and power calculations of future, adequately powered confirmatory studies.

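### Section 1.7.1 sets the kurtosis cut-off at the value of a normal distribution, so chance often decides which test and summary measure are used

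*Protocol article*

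**What the plan says.** Section 1.7.1 (Statistical Methods, Primary Endpoint) gives a numerical rule: a continuous variable is non-normal "if absolute skewness > 2 or kurtosis > 3". It names the software: "Statistical analyses will be conducted using StataNow18.5". The word "excess" does not appear.

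The label has these consequences:

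- **Continuous baseline characteristics (1.7.1):** independent t-test if normal, Mann-Whitney if not.
- **Pre-post cognitive change (1.7.1):** a paired t-test, or a transformation or non-parametric equivalent, is applied to "changes within all 25 participants". This step is also meant to show which cognitive subdomains respond most.
- **Responders versus non-responders on cognitive scores (1.7.1):** ANOVA and ANCOVA. Non-normal variables are transformed, with "median differences with percentage changes reported".
- **QEEG features (1.7.2):** independent t-test or Mann-Whitney, "depending on the normality of the variables". Section 1.7.2 has no definition of its own, so the one in 1.7.1 is the only one available.

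Section 4 (Limitations) describes the study as "intended to generate effect size estimates and feasibility data" for later trials and mentions an "anticipated imbalance in group sizes".

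**The concern.** Kurtosis is reported on two scales. The raw moment ratio is 3 for a normal distribution; excess kurtosis is 0. A limit of 3 is lenient on the excess scale. On the raw scale it is the normal value itself, so a normal variable falls on either side of it largely by sampling error. Taking more data does not help: the false-flag rate rises towards 50% as the sample grows.

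What is at stake is mainly reporting. The pilot is meant to supply effect sizes and to rank cognitive subdomains by response. If one subdomain is reported as a mean change and the next as a transformed, median or percentage change, and the difference comes from a noisy label, the ranking compares unlike quantities. For baseline characteristics and QEEG features, the label changes which p-value is reported.

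**Working it through.** **Inputs.** The cut-offs, the software and n = 25 come from section 1.7.1. Responder group sizes are not given; 8 to 17 per group is assumed. That Stata reports raw kurtosis is a software convention and is assumed, since the document does not state it. The plan gives no operating characteristic for its rule, so there is no figure to reproduce.

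**Formulas.** With m_k the k-th central sample moment (divisor n), skewness = m3 / m2^1.5 and raw kurtosis = m4 / m2². Excess kurtosis = raw kurtosis − 3, so a limit of 3 on the excess scale is 6 on the raw scale.

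**Step 1. Exactly normal data, literal rule** (400,000 simulated samples per size; 20,000 at n = 1000):

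| n | Flagged non-normal |
|---|---|
| 8 | 16.1% |
| 10 | 18.9% |
| 12 | 21.3% |
| 13 | 22.3% |
| 17 | 25.2% |
| 25 | 28.6% |
| 50 | 33.8% |
| 100 | 37.7% |
| 1000 | 45.7% |

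At n = 25 the skewness arm alone fires in 0.02% of samples, so kurtosis does all the work. The rate is below 50% only because sample kurtosis is biased downwards in small samples (mean 2.77, median 2.62 at n = 25). If the two groups are checked separately at 12 and 13, the chance that at least one is flagged is 1 − (1 − 0.213)(1 − 0.223) = 1 − 0.787 × 0.777 = 0.39.

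**Step 2. The excess reading.** With raw kurtosis > 6 (and the same skewness limit), the rate for normal data at n = 25 is 0.4%. With the bias-corrected estimator of excess kurtosis it is 1.1%. The two readings therefore differ by a factor of about 28.6 / 0.4 ≈ 70, or 28.6 / 1.1 = 26.

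**Step 3. Data that are not normal, n = 25:**

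| Distribution | Flagged, raw > 3 | Flagged, raw > 6 |
|---|---|---|
| Uniform | 0.5% | about 0% |
| 50:50 normal mixture, means 3 SD apart | 2.6% | under 0.1% |
| Exponential | 75% | 24% |
| Lognormal, log-SD 1 | 90% | 52% |

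The literal rule flags normal data about 28.6 / 2.6 = 11 times as often as this two-peaked mixture. Moving the limit to 6 cures the false flags but lets about 76% of exponential samples pass as normal.

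**Step 4. What this does to a ranking.** Take two subdomain change scores that are exactly normal and independent, each checked on 25 values. The chance that they receive different labels, and so different summaries, is 2 × 0.286 × 0.714 = 0.41. Real subdomain scores are integers and correlated, so this is an illustration and not a forecast.

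**Step 5. Inference** (normal data, 12 versus 13, one pooled check). Type I error of the two-stage choice is about 5.0%. The t-test and Mann-Whitney disagree at p < 0.05 in about 2% of null features and 5.8% at a standardised difference of 1.2. Power at that difference is 81.8% for t and 78.4% for Mann-Whitney.

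**The case against.** The strongest reply is that this is an undefined convention in an exploratory pilot: the authors may well have meant excess kurtosis, and little inference hangs on it. Several parts of that reply stand.

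- **QEEG ranking.** A reader might infer that QEEG features can no longer be compared on one scale. The protocol does not support that. Section 1.7.2 plans ROC analysis and a comparison of AUCs across biomarkers, which is rank-based and independent of the normality label. The median and percentage wording is in the cognitive analysis of 1.7.1; for QEEG features the label selects only the test.
- **Cognitive scores between groups.** These use ANOVA and ANCOVA, so the label does not decide t-test versus Mann-Whitney there. It triggers a transformation and a different summary.
- **Primary endpoint and error rate.** The responder proportion uses no normality rule, and type I error stays near 5%.
- **Two-peaked markers.** A marker that is two-peaked only because responders and non-responders differ can be normal within each group, and then treating it as normal is no error. Step 3 shows that the rule is a poor detector, not that such markers would be mishandled.
- **The 29%.** It is for exactly normal values checked once on all 25. MoCA and MMSE scores are integers from a narrow entry range. Educated participants take the MoCA and uneducated participants the MMSE, so a check within one test may use fewer than 25 values.

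What does not stand is the defence by intention. The article commits to a number, names the software, and says kurtosis without qualification. The two readings give very different rules, so the sentence needs correcting on either one.

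**Conclusion.** The point holds in limited form. On the literal text, the kurtosis limit labels about 29% of exactly normal variables non-normal at n = 25, and about 16% to 25% per group at 8 to 17. On the excess reading the figure at n = 25 is 0.4% to 1.1%. This rests on Stata reporting raw kurtosis, on exactly normal data, and on assumed group sizes.

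The consequence is that the test for baseline characteristics and QEEG features, and the method and summary for cognitive scores and subdomains, can switch by chance. The clearest harm is to the ranking of subdomains by response. It does not reach the responder proportion, the AUC comparison or the type I error. The rule should be corrected before the analysis, but it does not threaten the primary result.

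**What to change.** In section 1.7.1, remove the skewness and kurtosis switch and name in advance one test and one effect measure for each family of variables. For example: Mann-Whitney for all QEEG features, alongside the AUC already planned; and one paired method (such as the signed-rank test) with one summary for all cognitive subdomains. Section 1.7.2 then drops its reference to normality.

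The cost is a few sentences and no new data. Rank tests throughout lose about 3 points of power if the data are normal (81.8% to 78.4% in the case above).

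If a kurtosis rule is kept, state the scale and put the limit on the excess scale, that is, Stata kurtosis above 6. Say plainly that at n = 25 this misses about three quarters of exponential samples and practically all flat or two-peaked ones. A two-sided version, absolute value of (kurtosis − 3) above 3, adds nothing: raw kurtosis is never below 1, so the difference is never below −2 and the lower arm cannot fire.
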